# Protocol for a prospective, randomized study on neurophysiological assessment of lower urinary tract function in a healthy cohort

**DOI:** 10.1186/s12894-016-0188-9

**Published:** 2016-11-25

**Keywords:** Sensory evoked potential, Electroencephalography, Lower urinary tract, Urinary bladder, Urethra, Randomized, Lower urinary tract dysfunction, Current perception threshold, A-delta afferent fibers, Electrical stimulation

## Abstract

**Background:**

Lower urinary tract symptoms are highly prevalent and a large proportion of these symptoms are known to be associated with a dysfunction of the afferent pathways. Diagnostic tools for an objective and reproducible assessment of afferent nerve function of the lower urinary tract are missing. Previous studies showed first feasibility results of sensory evoked potential recordings following electrical stimulation of the lower urinary tract in healthy subjects and patients. Nevertheless, a refinement of the methodology is necessary.

**Methods:**

This study is a prospective, randomized trial conducted at Balgrist University Hospital, Zürich, Switzerland. Ninety healthy subjects (forty females and fifty males) without lower urinary tract symptoms are planned to be included in the study. All subjects will undergo a screening visit (including standardized questionnaires, 3-day bladder diary, urinalysis, medical history taking, vital signs, physical examination, neuro-urological examination) followed by two measurement visits separated by an interval of 3 to 4 weeks. Electrical stimulations (0.5Hz-5Hz, bipolar, square wave, pulse width 1 ms) will be applied using a custom-made transurethral catheter at different locations of the lower urinary tract including bladder dome, trigone, proximal urethra, membranous urethra and distal urethra. Every subject will be randomly stimulated at one specific site of the lower urinary tract. Sensory evoked potentials (SEP) will be recorded using a 64-channel EEG cap. For an SEP segmental work-up we will place additional electrodes on the scalp (Cpz) and above the spine (C2 and L1). Visit two and three will be conducted identically for reliability assessment.

**Discussion:**

The measurement of lower urinary tract SEPs elicited by electrical stimulation at different locations of the lower urinary tract has the potential to serve as a neurophysiological biomarker for lower urinary tract afferent nerve function in patients with lower urinary tract symptoms or disorders. For implementation of such a diagnostic tool into clinical practice, an optimized setup with efficient and reliable measurements and data acquisition is crucial. In addition, normative data from a larger cohort of healthy subjects would provide information on variability, potential confounding factors and cut-off values for investigations in patients with lower urinary tract dysfunction/symptoms.

**Trial registration:**

Clinicaltrials.gov; Identifier: NCT02272309.

## Background

Lower urinary tract symptoms (LUTS) such as urinary urgency, frequency and incontinence, imply a massive impairment of quality of life [1, 2].

LUTS are highly prevalent and a large proportion of LUTS are found to be associated with afferent nerve dysfunction [1, 3–5]. Assessment of afferent pathways in patients with LUTS is however a challenge. Specific diagnostic tools for an objective and reproducible measurement of bladder and urethral afferent nerve function are missing. Yet, filling cystometry (FC) is the standard method used in clinical practice for the assessment of bladder sensations [6–10]. Nevertheless, FC largely depends on the subjective perceptions and collaboration of the patient and is hence not an objective measurement of bladder sensations. In addition, the reliability of the FC is questionable and its variability and outcome resolution is too large to detect differences smaller than 100 mL [11, 12]. Moreover, FC only covers sensory information from the bladder but not from the urethra.

Current perception threshold (CPT) testing is another method of assessing sensations from the lower urinary tract (LUT). CPT testing is performed by asking the subject to indicate the onset of sensation when an increasing electrical stimulus is applied [13]. It was shown that this method is safe and well tolerated by healthy subjects and patients, but still, it provides only semi-quantitative information on sensations of the LUT [14–16]. In addition, local factors such as distance of electrodes to the mucosa and the mucosal condition itself can significantly affect CPTs [14, 17, 18].

A more objective and qualitative assessment of afferent nerve function are sensory evoked potentials (SEP) that are routinely used in neurophysiology to detect afferent nerve conduction qualities and integrity from different parts of the human body. By analysing the latencies and amplitudes of the SEPs (Fig. 1), information on nerve fiber integrity, conduction velocity and fiber type can be obtained [19, 20]. SEPs from the LUT would be useful not only for an assessment of LUT sensory function, to amend findings from previous investigations (i.e. history, neurologic examination, urodynamic examination), but also as a surrogate marker and outcome measure for treatments targeting afferent LUT pathways [21]. However, SEP measurements stimulating the LUT are more challenging than SEP measurements for cutaneous sites due to less direct control of electrode placement and potential changes of bladder volume with time, which can influence the SEP measurement. Furthermore, bladder SEPs may be less synchronized as they are likely mediated by poorly or non-myelinated fibres leading to less distinct summation of sensory potentials. Nevertheless, previous studies reported first feasibility results of SEP recordings from the LUT following electrical stimulation in healthy subjects [22–26] and patients [20, 27–29]. However, due to heterogeneous measurement settings and study populations, a clear conclusion cannot be drawn from these data. Currently, there is no standard for SEP measurements for the LUT. Hence, optimal stimulation and recording procedures as well as parameters still need to be determined.

**Fig. 1 Fig1:**
[figure not shown]
Example of a cortical LUT SEP recorded at Cz with the markers of the P1, N1 and P2 peaks and the corresponding latencies and peak-to-peak amplitudes

In this study we would like to advance the evaluation of viscero-sensory afferent pathways of the LUT and to refine the methodology of LUT SEPs in healthy subjects. We aim to get more knowledge on the impact of different stimulation parameters (e.g. stimulation frequency) on the reliability, shape, latency, amplitude and topographical distribution of SEPs recorded during electrical stimulation of the LUT. In a first step it is our goal to find a frequency that allows a faster acquisition of reliable SEPs than the previously used 0.5 Hz [25, 26] and to obtain normative LUT SEP data for the different localizations in the LUT from different gender groups. In a second step we aim to implement the optimized methodology into clinical practice to use it as an objective marker of pathological LUT conditions and to show distinction of healthy LUT neurophysiology and function.

## Methods and design

### Study design

This study is a prospective, randomized trial conducted as a single center study at the Spinal Cord Injury Center & Research Lab, Balgrist University Hospital, University of Zürich, Zürich, Switzerland. The study comprises three visits of which the first will be a screening visit followed by two measurement visits separated by an interval of 3–4 weeks (Fig. 2). The site of stimulation will be indicated by random group assignment (in females and males: dome, trigone, proximal urethra, distal urethra; in males additionally: membranous urethra). Consequently, ten females and ten males will be allocated to one localization. In addition, the frequencies used for the stimulation of the LUT and thereafter the SSEP measurements will be randomly applied.

**Fig. 2 Fig2:**
[figure not shown]
Study design and time schedule

### Study population and recruitment

The volunteers will be recruited via announcements at the University of Zürich, internet platforms (i.e. www.marktplatz.uzh.ch, www.tutti.ch, www.ronorp.net) and personal contacts. According to the inclusion- and exclusion criteria (Table 1), healthy female and male subjects without any LUTS will be included. Health is defined as the absence of any health troubles, as assessed by a complete medical history, standardized questionnaires, physical, neurological and neuro-urological examinations (Table 2). The absence of LUTS will be determined by uroflowmetry, a 3-day bladder diary and standardized urological questionnaires (FLUTS [30] /MLUTS [31]; Qualiveen [32]; IPSS [33]; Swiss German OAB [34]) (Table 2).

**Table 1 Tab1:** Inclusion and exclusion criteria for healthy female and male volunteers

Inclusion criteria	Exclusion criteria
Written informed consent	Any lower urinary tract symptoms^d, f, c^
Good mental^a^ and physical health^c^	Any neurological or urological pathology ^e, f, c^
Age > 18 years^c^	Current pregnancy^bc^, lactation^c^
No regular intake of medication^c^	UTI^b, c, f^
Bladder capacity <150 mL or SDV already at 60mL^d, e, g^	Hematuria^b^
Number of voids per day <8, number of voids per night <2^d, f, c^	Any anatomical anomaly/malignancy of the LUT or genitalia ^e, c^
	Any previous pelvic, spine or craniocerebral surgery^c^

*LUT* lower urinary tract, *SDV* strong desire to void, *UTI* urinary tract infection

^a^assessed by MoCA and HADS; ^b^excluded by urine dipstick test; ^c^assessed by history taking; ^d^assessed by 3-day bladder diary; ^e^assessed by neuro-urological examination ^f^assessed by standardized urological questionnaires (FLUTS, MLUTS, IPSS, Qualiveen, Swiss-German OAB questionnaire); ^g﻿^assessed by uroflowmetry

**Table 2 Tab2:** Overview of the screening procedure

Tests	Questionnaires / Bladder diary
Urine dipstick	FLUTS [28] / MLUTS [29]
Pregnancy	Qualiveen [30]
	ICIQ-LUTSqol [35]
	IPSS [31] (only for males)
**Examinations**	Swiss German OAB questionnaire (short form) [32]
Bulbocavernosus reflex	FSFI [34] / IIEF [33]
Anal reflex	HADS [36]
Pin-prick of S2-S5 dermatomes	MoCA [37]
Uroflowmetry	3-day bladder diary
Assessment of medical history	
Physical examination	

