### Investigations and procedures

#### Screening (visit one)

The content and purpose of the study will be explained in written and oral form to all recruited subjects. Those subjects providing written informed consent will be screened for in- and exclusion criteria by using the tests, questionnaires, and examinations listed in Table 2. Subjects who are eligible for study participation according to the in- and exclusion criteria (Table 1) will be invited for visit two and three (Fig. 2).

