#### Measurement visits (visit two and three)

Prior to each measurement, the urine of the volunteers is analyzed to exclude signs suggestive for asymptomatic bacteriuria, microhaematuria, and (in women only) pregnancy. Both measurements consist of a resting electroencephalogram (EEG) measurement followed by recordings of SEPs elicited by transurethral electrical stimulation at a specific LUT site indicated by the group assignment. Each measurement includes recordings of the electrooculogram (left and right eye), electrocardiogram, and electroencephalogram using a 64 Ag/AgCl surface electrodes system comprising a cap-based extended international 10–20 montage (Easy cap, Easy cap GmbH, Herrsching, Germany). Electrode impedances are constantly kept below 20kΩ. Six additional electrodes are placed at Cpz (reference: Fz), C2 (reference: Fz) and L1 (reference: iliac crest), respectively, for segmental assessment. LUT electrical stimulation will be applied transurethrally with a custom-made 14 Ch catheter (Unisensor AG, Attikon, Switzerland), using frequencies between 0.5Hz and 5Hz (bipolar, square wave, pulse width 1 ms). Stimulation intensities are adapted to the 3 to 4× CPT, which is determined using the method of limits prior to each SEP measurement [13]. The catheter includes platinum electrodes and a radiopaque marker, which allows precise catheter positioning under fluoroscopic guidance. After each stimulation, the bladder will be emptied and filled with 60 mL of contrast medium (Ultravist® 150^TM^, Bayer AG, Switzerland). Consequent to LUT SEPs, SEPs elicited by transcutaneous stimulation of the tibial and pudendal nerves will be recorded in random order. These standard neurophysiological measurements will serve as comparators to the LUT SEPs. Visits two and three will be performed identically with an interval of 3 to 4 weeks (Fig. 3).

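### Table 1 prints small bladder capacity or an early strong desire to void as an inclusion criterion, which contradicts the healthy, symptom-free cohort the study is meant to recruit

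*Protocol article*

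**What the plan says.** Table 1 of the protocol article has an inclusion column and an exclusion column. The fifth inclusion entry is "Bladder capacity <150 mL or SDV already at 60mL", where the table's key expands SDV as "strong desire to void". The entry carries footnotes naming the bladder diary, the neuro-urological examination and uroflowmetry as the means of assessment. The next inclusion entry is "Number of voids per day <8, number of voids per night <2". The first entry in the exclusion column is "Any lower urinary tract symptoms".

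The text above the table says that "healthy female and male subjects without any LUTS will be included". The Background describes the symptoms meant: "Lower urinary tract symptoms (LUTS) such as urinary urgency, frequency and incontinence".

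The section on screening makes the table operative: "Subjects who are eligible for study participation according to the in- and exclusion criteria (Table 1) will be invited for visit two and three". In the section on the measurement visits, after each stimulation "the bladder will be emptied and filled with 60 mL of contrast medium". The abstract and the Discussion say that the study should yield normative values in healthy subjects and cut-offs for later use in patients. The trial status section reports that the first subjects have already been included and investigated.

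**The concern.** An inclusion criterion is a condition every participant must meet. As printed, this one requires either a capacity below 150 mL or a strong desire to void by 60 mL. A volunteer with a larger capacity and no early desire, whom the rest of the article leads one to expect in a healthy cohort, would fail it.

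What is at stake is whom the normative values describe. If the row were followed as written, latencies, amplitudes and cut-offs offered as a healthy reference would come from people selected for small capacity or early desire to void. Patients with lower urinary tract symptoms are later to be compared against those values. Anyone repeating the study, or judging whether its cut-offs apply to their own patients, would also take the eligibility rule from this table.

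**Working it through.** The article gives no figure for this point that could be reproduced, so the check is mainly a comparison of its own statements.

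**1. Is the row really in the inclusion column?** Table 1 has six inclusion and seven exclusion entries. The disputed row has an entry on both sides (its exclusion partner is hematuria), the rows above and below are in order, and only the last row has an empty inclusion cell, as six against seven requires. A fault in reading the table is therefore unlikely.

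**2. What does the row require?** Let A be capacity below 150 mL and B be strong desire to void already at 60 mL. As an inclusion criterion the row admits a volunteer if A or B holds. It rejects a volunteer if neither holds.

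**3. Does that fit the rest of the article?**

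| Statement | Direction |
|---|---|
| Disputed row, Table 1 | Requires A or B |
| Population sentence, same section | Healthy, no lower urinary tract symptoms |
| First exclusion entry, Table 1 | Any such symptom excludes |
| Next inclusion entry, Table 1 | Upper limits on voids by day and night |
| Abstract and Discussion | Healthy reference values and cut-offs |

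Only the disputed row points away from normal storage function. Nothing elsewhere in the article states it the other way round or corrects it.

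**4. What does the 60 mL figure suggest?** The volume in limb B is the volume used to refill the bladder at the measurement visits. A subject qualifying through B would have a strong desire to void at that volume. The match suggests that the row was written to keep such people out.

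**5. Can the row and the void limits both be met?** Fewer than 8 voids by day and fewer than 2 by night allow at most 7 + 1 = 8 voids in 24 hours. Assume that capacity caps every voided volume. A person qualifying through limb A then passes less than 8 × 150 mL = 1200 mL in 24 hours. The article gives no urine output to set against this. The two entries pull against each other, but they do not exclude each other. The main point does not depend on this step.

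**The case against.** The strongest reply is that this is a plain slip in a condensed article. The table's title, the exclusion beside the row and the population sentence all say who is wanted, and an investigator at this single centre would be unlikely to recruit the reverse. The full protocol is not shown and may state the criterion correctly. Much of this stands: a slip is the most likely explanation, and harm depends on the row being applied literally. It does not remove the point, because the article states the rule wrongly rather than leaving it out, and names Table 1 as what decides eligibility.

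Three stronger readings are tempting, and the article does not support them.

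- *A reader might infer that almost nobody could be eligible.* The article never says that a capacity below 150 mL, or a strong desire to void at 60 mL, is itself a lower urinary tract symptom. The overlap between the row and the symptom exclusion is therefore unknown, and step 5 shows tension only.
- *A reader might infer that, if the row were ignored, such people would enter freely.* No other entry in Table 1 names capacity or the volume at strong desire. But the symptom exclusion, judged by diary, questionnaires and history, would probably already remove many of them.
- *A reader might infer a separate conflict with the recording procedure.* The article places the 60 mL filling after each stimulation and does not say in so many words that it precedes each recording. The shared volume is better used as evidence of what the row was meant to do.

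**Conclusion.** The point holds as an internal contradiction in an operative rule. One row of Table 1, as printed, selects people whom the rest of the article gives every reason to leave out. The wording applies to all 90 planned subjects (50 men and 40 women); that is its reach, not a count of subjects affected.

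The conclusion rests on two readings. The first is that the inclusion column lists conditions to be met, which is its ordinary meaning. The second is that small capacity or an early strong desire to void is out of keeping with the intended cohort. The article does not say this outright; it is inferred from the symptom-free definition, the symptom exclusion, the 60 mL filling volume and the normative purpose.

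Nothing in the article shows that the error is in the full protocol or the screening form, or that any enrolled subject was screened by the literal wording. No effect on sample size, randomization or analysis is claimed. The row should still be corrected, because the value of a normative study depends on knowing who was eligible.

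**What to change.** Reconcile the row with the healthy-cohort definition in either of two ways, leaving the thresholds as the sponsor set them:

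- move it unchanged to the exclusion column, so that meeting either limb excludes; or
- keep it in the inclusion column and negate it as a whole. The negation of A or B is not-A *and* not-B, so the joining word must change with the inequality.

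Then confirm two things: that the full protocol and the screening form carry the intended reading, and that subjects already included were screened under it. If any were not, they should be identified before their recordings enter the normative values.

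The cost is a correction to one table row, the same correction to the screening form only if it carries the same wording, and a check of existing screening records. No new procedure or measurement is needed.

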### Investigations and procedures

#### Screening (visit one)

The content and purpose of the study will be explained in written and oral form to all recruited subjects. Those subjects providing written informed consent will be screened for in- and exclusion criteria by using the tests, questionnaires, and examinations listed in Table 2. Subjects who are eligible for study participation according to the in- and exclusion criteria (Table 1) will be invited for visit two and three (Fig. 2).

#### Measurement visits (visit two and three)

Prior to each measurement, the urine of the volunteers is analyzed to exclude signs suggestive for asymptomatic bacteriuria, microhaematuria, and (in women only) pregnancy. Both measurements consist of a resting electroencephalogram (EEG) measurement followed by recordings of SEPs elicited by transurethral electrical stimulation at a specific LUT site indicated by the group assignment. Each measurement includes recordings of the electrooculogram (left and right eye), electrocardiogram, and electroencephalogram using a 64 Ag/AgCl surface electrodes system comprising a cap-based extended international 10–20 montage (Easy cap, Easy cap GmbH, Herrsching, Germany). Electrode impedances are constantly kept below 20kΩ. Six additional electrodes are placed at Cpz (reference: Fz), C2 (reference: Fz) and L1 (reference: iliac crest), respectively, for segmental assessment. LUT electrical stimulation will be applied transurethrally with a custom-made 14 Ch catheter (Unisensor AG, Attikon, Switzerland), using frequencies between 0.5Hz and 5Hz (bipolar, square wave, pulse width 1 ms). Stimulation intensities are adapted to the 3 to 4× CPT, which is determined using the method of limits prior to each SEP measurement [13]. The catheter includes platinum electrodes and a radiopaque marker, which allows precise catheter positioning under fluoroscopic guidance. After each stimulation, the bladder will be emptied and filled with 60 mL of contrast medium (Ultravist® 150^TM^, Bayer AG, Switzerland). Consequent to LUT SEPs, SEPs elicited by transcutaneous stimulation of the tibial and pudendal nerves will be recorded in random order. These standard neurophysiological measurements will serve as comparators to the LUT SEPs. Visits two and three will be performed identically with an interval of 3 to 4 weeks (Fig. 3).

**Fig. 3 Fig3:**
[figure not shown]
Flowchart of the measurement visits (visits two and three)

#### Follow-up

Two to three days after each measurement visit, a follow-up interview is performed to evaluate the general well-being of the volunteers. In case of any side effects, such as dysuria, the subjects are appointed to an extra medical visit for further evaluation, investigation and, if necessary, medical treatment.

### Safety

During the first visit, all subjects are carefully screened to exclude subjects with neurological and/or urological pathology or any regular medication intake. At the beginning of every visit an urinalysis and pregnancy test (in females only) is performed to exclude signs suggestive for asymptomatic bacteriuria, microhaematuria and pregnancy, respectively. Pregnancy leads to study exclusion and referral to a gynecologist for further evaluation. In case of a positive urine dipstick test suspicious for asymptomatic bacteriuria or urinary tract infection (UTI), the measurement will be postponed until the dipstick test result becomes negative or UTI has been treated. In case of a dipstick test indicating microhaematuria, subjects can choose to repeat the test at a later time-point or to directly have the result verified by clean catheterization. If clean catheterization still indicates microhaematuria, subjects will be excluded from study participation and referred to their general practitioner or urologist for further evaluation.

Two or three days after the measurement visits, a follow-up interview will be conducted to assess general well-being and document possible adverse events or symptoms. In case of an adverse event, additional tests or medical interventions will be initiated as necessary and subjects might be referred to a general physician or medical specialist for further investigations and/or treatment. All responsible authorities will be informed about any adverse events (AE) or severe adverse events (SAE). These events will be observed and followed until complete cure. To decrease the radiation dose during visits two and three, we will not perform full radiographs but fluoroscopy with a reduced field of view focusing on the LUT only. For a protection of the male gonads, men will wear a gonad shielding.

